### Recruitment {15}

The patients posted for surgery, elective or emergency, under general anesthesia requiring endotracheal intubation will be assessed for eligibility criteria from the preoperative period. They will be recruited after they provide valid consent for the study. It is estimated that with the volume of surgeries and new trainees the institute sees every year, the sample size will be easy to achieve. Moreover, it is a routine procedure. Being a thesis topic, it was discussed in the departmental meeting and all 14 faculty and 31 residents were made aware of the protocol to make sure none of the eligible GA cases with ETT intubation by a trainee is missed.

### Assignment of interventions: allocation

#### Sequence generation {16a}

The enrolled participants will be randomized to one of two groups. A web-based random number generator (www.randomizer.org) will be used for generating codes under a simple randomization scheme. Participants will be randomized to either of the two groups at a 1:1 allocation ratio according to the random codes assigned by the web.

#### Concealment mechanism {16b}

The random codes will be written on a piece of paper and put in opaque brown envelopes which will be sealed. Once a patient has been enrolled, the operating room’s technical staff will open an opaque, sealed envelope containing the group allocation and mark the ETT accordingly. Allocation concealment will be ensured, as the randomization code will not be released until the patient has been recruited into the trial, which takes place after all baseline measurements have been completed in the pre-anesthesia checkup, the evening before surgery.

#### Implementation {16c}

Neither front-line care providers, investigators, nor participants will be aware of whether the next eligible participants will be receiving treatment or control intervention. One of the team members will enroll the participants and leave the set, sequentially numbered, generated by the research assistant, sealed opaque envelopes with the OT technician (OTT) responsible for anesthesia for the patient. The OTT will not be a part of the research team and will open the sealed envelopes to read the randomization sequence, which will be matched with the random number sequence generated earlier. He will be the one to mark the ETT at the designated site as per the number picked and the group it belongs to. The intubator will be asked to hold at the marked site after he/she confirms the optimal CL view. The assessors calculating time timings from the video will be blinded to the group the video belongs to.

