**Methods:**

ASA 1–2 patients (>18 years) posted for surgery under general anesthesia, undergoing supervised intubation by anesthesia trainees (experience < 18 months), will be included. Patients with an anticipated difficult airway or unanticipated difficulty—CL grade 3 or 4 requiring the use of airway adjuncts—will be excluded. Patients will be randomized by a computer-generated number list, and allocation concealed with opaque sealed envelopes. The two sites for holding the ETT will be group 1 at 19 cm and group 2 at 24 cm. ETT marked at the selected site will be handed by the technician once the optimum position of the table, patient, and laryngoscopic view is confirmed by the intubator. The entire procedure will be video recorded. Two blinded assessors will independently review the videos to document the time to intubation and intubation difficulty score. A postoperative sore throat will be recorded.

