### Trial design {8}

This will be a randomized, controlled, surgeon-, patient-, and assessor-blinded single-center equivalence trial with two parallel groups and a primary endpoint of time to intubation during direct laryngoscopy for general anesthesia. Randomization will be performed as simple randomization with 1:1 allocation.

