##### Personnel

1. The consultant anesthetist and trainee will position the patient and prepare for intubation.

2. The operation theater technician (not a part of the research team) will select a sealed envelope after the patient enters the theater and the WHO checklist is completed. He will then mark the endotracheal tube at the site the patient has been randomized to19 or 24 cm with a transparent sticker.

3. A trainee technician (not a part of the research team) will be positioned in a way such that the entire process is visible and will video record the procedure.

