### Criteria for discontinuing or modifying allocated interventions {11b}

If the intubator cannot intubate at the given tube mark, he will be allowed to change the site of grip—the site change will be noted from the video. If he/she still fails, the consultant can take over.

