### Assignment of interventions: blinding

#### Who will be blinded {17a}

The patient, the outcome assessor, and the data analyst will be blinded to the study intervention.

The intraoperative anesthesia team will not be blinded to the study.

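### Assessor blinding is claimed for the video readers but not secured, because the footage they read shows the randomised feature, the grip site

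*Protocol article*

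**What the plan says.** The blinding claim appears throughout the protocol article. Trial design {8} describes the trial as "surgeon-, patient-, and assessor-blinded". Implementation {16c} states: "The assessors calculating time timings from the video will be blinded to the group the video belongs to". Who will be blinded {17a} goes further, to the intervention itself: "The patient, the outcome assessor, and the data analyst will be blinded to the study intervention". The abstract's Methods, the secondary objectives under {7}, Outcomes {12}, the participant timeline {13} and Plans for assessment and collection of outcomes {18a} all describe video readers or the ease assessor as blinded or unaware of the allocation.

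The contrast under test is given in the abstract: "The two sites for holding the ETT will be group 1 at 19 cm and group 2 at 24 cm". Under Personnel in {11a}, a trainee technician is to be "positioned in a way such that the entire process is visible and will video record the procedure". Outcomes {12} starts TTI at the moment the tube is held and ends it when the laryngoscope is removed. If the intubator changes the grip, {11b} provides that "the site change will be noted from the video". The dropout criteria under {10} exclude any procedure with a change of grip after the tube is held. They also exclude any video on which the assessors disagree about the time or the method.

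**The concern.** Withholding a group code blinds a reader only if the material being read does not itself reveal the group. Here the treatment is a hand position and the material is a film of the hand. If readers can work out the arm, their judgements could drift with their expectations, and the report would claim a protection that the design does not provide.

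This matters most where judgement is greatest: the assessor's ease rating, IDS items such as normal versus increased lifting force, and decisions that remove a patient from the final analysis. The ease rating deserves particular care. {17a} says openly that the anesthesia team is not blinded, so the intubator's and faculty's ratings are unblinded, and the blinded assessor is the only protection claimed for that outcome.

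**Working it through.** No figure in the plan bears on blinding, so the main check sets the sections side by side.

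| What the reader does or sees | Where | Does it expose the grip? |
|---|---|---|
| Watches footage of the entire procedure | Personnel, {11a} | Yes, potentially |
| Starts the clock when the tube is held | Outcomes {12} | Yes: the start event is the hand taking the tube |
| Judges the method of intubation | Dropout criteria, {10} | Yes: the grip is part of the method |
| Receives videos under identifier codes | {18a} | The code hides the label, not the image |
| Sees a transparent sticker on the tube | Personnel, {11a} | The sticker hides neither hand nor grip |

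No section describes cropping, blurring or any other way of hiding the hand or tube. The explanation for the holding sites under {6b} says they were derived from a pilot that video recorded intubations by 54 experienced anesthesiologists (mean site 21.3 cm, SD 2.5 cm). That suggests, without proving, that the grip site can be read from film. The two arms are 24 − 19 = 5 cm apart.

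The documents do not say outright that the assessor's ease rating is made from the video. The timeline places it after extubation, and {18a} has a blinded assessor from outside the team analysing the videos, so I take the footage to be its source.

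**Illustration for TTI.** The size of any differential reading bias is an assumption; the documents give none. The SD (4.07 s), the 149 per arm, the 180 recruited per arm and the 5% level come from Sample size {14}. I use 149 only as the plan's stated number; whether it delivers the stated power is a separate question.

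- Standard error of the difference: SE = SD × √(2/n). For n = 149, 4.07 × √(2/149) = 0.472 s. For n = 180, 4.07 × √(2/180) = 0.429 s.
- With a bias b between arms and no true difference, two-sided type I error = Φ(−1.96 + b/SE) + Φ(−1.96 − b/SE).

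| Assumed bias between arms | 149 per arm | 180 per arm |
|---|---|---|
| 0.1 s | 5.5% | 5.6% |
| 0.25 s | 8.3% | 9.0% |
| 0.5 s | 18.5% | 21.4% |

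Only a bias that differs between arms counts. A timing habit common to both arms cancels.

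**The case against.** The strongest reply is that nothing in the protocol proves a reader can identify the arm. No section gives the camera's angle, distance or resolution, and a 5 cm difference in grip may not be legible in every clip. A reader might infer from the text that assessor blinding simply does not exist; the documents do not support that. They support the narrower statement that it is claimed and not secured.

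The plan also has safeguards. Under {18a} the reader from the investigating team is not told the allocation, and the other reader comes from outside it. Outcomes {12} adds independent reading, averaging, a third person from outside the team to settle disputes, and an ease rater with no connection to the study. These limit random error and some partiality. They do not hide the grip, and averaging does not remove an expectation that both readers share. The dropout criteria would exclude disputed videos rather than have them settled, so it is also unclear when the third person acts.

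Two further inferences are tempting and should not be drawn. {11b} does not say who notes a change of grip site, so that task cannot be assigned to the timing readers; what the text gives them is the judgement on method. And Background {6a} attributes the belief that a farther grip is better to the senior investigator and peers; nothing says that the team's video reader is that person.

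Finally, holding the tube and removing the laryngoscope are fairly objective events, and a bias of 0.1 s would hardly move the error rate. That stands, and it is why TTI is not the main exposure.

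**Conclusion.** The concern holds in this form: the readers are kept from the allocation code but not from the grip, so the blinding stated in {8}, {16c} and {17a} is not secured by the procedures described. The principal exposure is the assessor's 0–5 ease rating, the subjective IDS items and the exclusions for grip or method. No size can be put on these from the documents.

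TTI is less exposed. The inflation to between about 5.5% and 18.5% at 149 per arm depends wholly on the assumed differential bias of 0.1 to 0.5 s and on the pilot SD. It is not evidence that such a bias will occur, nor that the primary result will be invalid. The conclusion also assumes that no masking step exists. If the footage is in fact masked, the protocol should say so, and should say how method and grip are then judged.

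**What to change.** Correct the claim wherever it is made for video readers or the ease assessor: the abstract's Methods, the secondary objectives under {7}, {8}, {12}, {13}, {16c}, {17a} and {18a}. Suitable wording: *not told the allocation, but able to see the grip on the video*. The claims for the patient and the data analyst are not affected by this point.

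Report the assessor's ease rating, the IDS and the video-based exclusions as not reliably blinded, and treat the assessor's ease rating as supportive only.

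Keep the current TTI definition. Moving its start point would change the primary outcome in a trial already recruiting. Masking the hand and tube would obstruct the checks on grip change and tube manipulation in {10} and {11b} unless another reviewer were added. Neither is needed to make the description accurate.

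The cost is wording, plus notification through the route in {25} if the standing of the ease rating is treated as a change to outcomes or analyses. The downside is a less favourable description of the trial's protection against bias.

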### Assignment of interventions: blinding

#### Who will be blinded {17a}

The patient, the outcome assessor, and the data analyst will be blinded to the study intervention.

The intraoperative anesthesia team will not be blinded to the study.

#### Procedure for unblinding if needed {17b}

In infrequent circumstances which may hamper the patient’s safety, unblinding may be done.

### Data collection and management

#### Plans for assessment and collection of outcomes {18a}

All demographic and clinical data will be entered into paper-based case record forms.

Videographic data taken at the time of intubation will be stored with identifier codes. They will be analyzed separately by an experienced anesthesiologist from the investigating team who is not aware of the group allocations and a blinded assessor who is not part of the study team.

The case record forms can be collected by emailing the corresponding author of this manuscript.

#### Plans to promote participant retention and complete follow-up {18b}

As the patient will be with the same anesthesia team, retention will not be a significant concern once recruited. However, at the time of writing this manuscript for protocol submission (midway of the study), the COVID pandemic started—this affected the methodology of intubation—limiting the number of personnel in the room and the use of PPE, which might have affected the primary outcome; the number of intubations had also reduced, so we approached the IEC for allowing the inclusion of patients undergoing emergency surgeries ( non-COVID suspect) and those with any Mallampati scores ( previously we were excluding those with MPG III and IV) and for an interim analysis to assess for stopping the trial or amendment in sample size.

### Data management {19}

All data (case record forms and videos) will be stored in a password-protected computer in an Excel spreadsheet for further analysis. All measures will be taken to provide a backup of stored data in case of data loss.

### Confidentiality {27}

The participants’ identity and sensitive personal details will remain confidential with the principal investigators and will not be disclosed in any form.

### Plans for collection, laboratory evaluation, and storage of biological specimens for genetic or molecular analysis in this trial/future use {33}

No biological specimens will be collected in this study.

### Statistical methods

#### Statistical methods for primary and secondary outcomes {20a}

A researcher blinded to the group allocation will perform the statistical analysis of all randomized patients using the SPSS for Windows software (ver. 26.0; SPSS Inc., Chicago, IL, USA) on completion of the study.

Flowchart

For presenting the demographic data, the categorical data (like gender, SA status, gender) will be presented as a percentage of the total, while the quantitative data will be presented as means or medians with standard deviations or interquartile range. The data will be tabulated with standardized differences reported between groups.

The primary outcome will be described in seconds. The descriptive statistics that will be used is a standardized difference of means or proportions accordingly. All the secondary outcomes data, namely time to intubation and the IDS, are quantitative and will first undergo a normality test either the Shapiro-Wilk test or the Kolmogorov-Smirnov test to check the normality of the quantitative variables’ distribution. After this, the Mann-Whitney *U* test or independent *t*-test will be used, depending on whether the data is parametric or non-parametric, including the primary outcome variables. Accordingly, the data will be represented as mean with standard deviation or median with interquartile range.

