#### Objectives

##### Primary objective

To compare the time to intubation (TTI) between two groups of trainees holding the ET at two different (predetermined) sites.

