### Eligibility criteria {10}

The participants included in the study will be:
i.Patient: Adult patients (age > 18 years) with ASA I to II functional status undergoing elective/emergency surgical procedures under general anesthesia who can understand and provide valid consent for the procedure. The exclusion criteria will be patients less than 18 years of age, American Society of Anesthesiologists (ASA) > 2 functional status, patients having Cormack Lehane (CL) grading more than 2 on direct laryngoscopy, use of airway adjuvants, and refusal to give consent for the study.ii.Intubator: Intervention (intubation) will be performed by trainee anesthesia residents who have less than 18 months of experience. As a part of the curriculum, training in the theory of airway management and mannikin intubations will ensure that all the trainees have experience of a minimum of 40 intubations on mannikins or patients. A consultant anesthetist will supervise all intubations per protocol.iii.Procedure: All procedures will be video recorded from the time patient is positioned after induction, and the laryngoscope is asked for, to after confirmation of correct tube position (this may be visual, auscultatory, or EtCO2 guided). Procedures where the trainee deviates from the methodology, improper table position, CL grade found > 2, use of a bougie, stellate, or other airway adjuncts, or take-over by the consultant (unanticipated difficult airway), will be video recorded but excluded from the analysis. This will reduce confounding the time to intubation due to poor visualization of the laryngeal inlet.

A few cases will be tried with a Go-Pro camera, hoping to ascertain data for the exact laryngoscopy view (with the understanding that the visual axis of the camera will not be identical to the LEI, and the forehead mounted camera might make the process more cumbersome for the trainee).

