**Assessments**					
Demographic characteristics	**X**				
Airway assessment	**X**	X			
Experience of the intubator (in months)		X			
Time of holding of ET (T1)			**X**		
Time of removal of laryngoscope (T2)				**X**	
Time to intubation (from T1 to T2)			**X**	**X**	
Intubation difficulty score			**X**		
Any change in the site of holding the tube			**X**		
Videography during intubation		**X**	**X**	**X**	
Ease of intubation on Likert scale by the intubator			**X**	**X**	
Ease of intubation assessed by faculty			**X**	**X**	
Ease of intubation assessed by a blinded assessor					**X**
Incidence of airway trauma (bleeding/sore throat )			**X**		**X**

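### The primary test is unadjusted and picked by an open-ended normality pre-test, and no effect with a confidence interval on the 20% scale is named; the cost is precision and interpretability, not validity

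*Protocol article*

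**What the plan says.** Statistical methods {20a} states that the quantitative outcomes "will first undergo a normality test either the Shapiro-Wilk test or the Kolmogorov-Smirnov test". A Mann-Whitney U test or an independent t-test then "will be used, depending on whether the data is parametric or non-parametric, including the primary outcome variables". That paragraph lists TTI among the secondary outcomes, but its last clause brings the primary outcome under the same rule. The effect summary is described as follows: "The descriptive statistics that will be used is a standardized difference of means or proportions accordingly". Group results are to be shown as mean with SD or median with interquartile range. No covariate, operator or period term is named, and neither is a confidence interval.

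Other sections bear on this:
- Participant timeline {13} records the intubator's experience in months, before intubation.
- The Discussion accepts that trainees' first-pass success depends on experience.
- Section {18b} says of the pandemic that "this affected the methodology of intubation", that the primary outcome might have been affected, and that wider eligibility was sought mid-trial.
- Sample size {14} sizes and clinically justifies the trial by a 20% difference in TTI, and also names a difference of 1 s.

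**The concern.** There are three weaknesses.

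- **The data choose the test, and the chooser is not fixed.** Shapiro-Wilk and Kolmogorov-Smirnov differ in sensitivity, so the primary test can depend on which one the analyst runs.
- **The target scale is not estimated.** The clinical argument concerns a 20% change in TTI. A Mann-Whitney p-value gives no percentage or difference in seconds, and a standardized difference labelled descriptive does not fill that gap.
- **Known sources of variation stay in the error term.** Experience is collected and then unused. The protocol itself suspects a period effect, and the analysis does not take it up.

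At stake is whether the trial can say how much faster one grip site is, and with what precision.

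**Working it through.** **Inputs.** Sample size {14}: mean 8.83 s, SD 4.07 s, two-sided 5%, 85% power, normal approximation, 149 per group. The share of TTI variance explained by trainee, experience and period is not given. I assume 0.1 to 0.3.

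**1. The plan's own figure.** n per group = 2 × SD² × (1.960 + 1.036)² / Δ².
- Δ = 1 s: 2 × 16.56 × 8.98 / 1 = 297.4, so 298 per group.
- Δ = 20% × 8.83 = 1.766 s: 297.4 / 3.119 = 95.4, so 96 per group.

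Neither gives 149 per group. That is a separate matter. Below I take 149 per group as given and show both effects.

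**2. Unadjusted power.** SE = 4.07 × √(2/149) = 0.4715 s. Power = Φ(Δ/SE − 1.960).
- 1 s: Φ(2.121 − 1.960) = 56.4%.
- 1.766 s: Φ(3.745 − 1.960) = 96.3%.

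**3. Power if a share ρ of the variance is removed.** Replace SD by SD × √(1 − ρ).

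| ρ | SD (s) | 95% CI half-width (s) | Power, 1 s | Power, 1.766 s |
|---|---|---|---|---|
| 0 | 4.07 | 0.92 | 56.4% | 96.3% |
| 0.1 | 3.86 | 0.88 | 60.9% | 97.7% |
| 0.2 | 3.64 | 0.83 | 65.9% | 98.7% |
| 0.3 | 3.41 | 0.77 | 71.7% | 99.4% |

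**4. Simulation.** The formula is slightly optimistic, because trainee effects must be estimated and simple randomisation leaves uneven allocation within trainees. With 298 patients and 15 or 31 trainees, power for 1 s went from about 56–58% unadjusted to 64–65% at an intraclass correlation (ICC) of 0.2 and 66–71% at 0.3.

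A second simulation used log-normal TTI with log SD = √ln(1 + (4.07/8.83)²) = 0.439, 20 trainees (assumed) and 1,500 runs per setting. It compared the planned two-stage rule with a trainee-adjusted analysis of log TTI:

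| Ratio | ICC | Two-stage rule | Adjusted log model |
|---|---|---|---|
| 1.113 (1 s) | 0 | 55% | 54% |
| 1.113 | 0.1 | 55% | 58% |
| 1.113 | 0.3 | 54% | 66% |
| 1.20 | 0 | 92% | 92% |
| 1.20 | 0.1 | 94% | 95% |
| 1.20 | 0.3 | 94% | 98% |

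With no true difference, the two-stage rule rejected in 5.1–5.5% of runs, within simulation error of 5%.

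**5. Which test the pre-test selects.** Rejection rates with 149 values at the pilot mean and SD (Kolmogorov-Smirnov in Lilliefors form):

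| Assumed shape | Shapiro-Wilk | Kolmogorov-Smirnov |
|---|---|---|
| Log-normal | 100% | 96% |
| Gamma | 99% | 73–76% |
| Weibull | 67% | 25% |
| Near-normal, truncated at 1 s | 24% | not run |

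Mann-Whitney is the likely end point for clearly skewed times. For milder shapes the outcome depends on which pre-test is used.

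**The case against.** The strongest reply is that an unadjusted comparison in an individually randomised trial is legitimate, that the pre-test did no measurable harm to error rates, and that covariates are often left to a SAP. The first two points stand. The third does not answer the concern: the article states the test and the rule for choosing it, so this is a method fixed in the text.

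Several stronger readings are tempting, and the documents do not support them.

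- **Clustering invalidates the test.** The primary objective speaks of a comparison "between two groups of trainees holding the ET at two different (predetermined) sites", which a reader might take to mean that trainees are the unit. Patients are randomised, 1:1 and individually (Trial design {8}, Sequence generation {16a}). Ignoring trainee therefore costs precision and does not inflate type I error.
- **At most 31 residents do all 360 intubations, about 12 each.** Recruitment {15} says that "all 14 faculty and 31 residents were made aware of the protocol". That is a headcount of people informed. The same section counts on new trainees each year, and intubators must be "trainee anesthesia residents who have less than 18 months of experience", so the pool turns over and not all 31 need qualify.
- **The pre-test is certain to reject.** Mean and SD do not fix the shape. A normal distribution with these values has only Φ(−8.83/4.07) = 1.5% below zero.
- **No effect can be obtained at all.** TTI is to be described in seconds, and a difference can be derived from group means if the t-test is chosen. The gap is narrower: no estimate with an interval on the target scale is named.
- **A general power gain.** One could quote the gain at 1.41 s, the difference that 149 per group detects at 85% power. The protocol names no such effect. At its 20% target there is little left to gain.

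**Conclusion.** The point holds as a weakness in precision and interpretability. It is worth correcting, but it is not a validity flaw. Two parts do not depend on any assumed ICC: the choice of primary test is left to an unspecified pre-test, and no effect with a confidence interval is tied to the 20% target. That a rank test will result is likely, conditional on right skew.

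The precision part rests on an assumed share of explained variance. Near 0.1 the gain is small (3 to 5 percentage points of power for 1 s), and for a true 20% effect it hardly matters. For 1 s at a share of 0.2–0.3, power rises from about 56% to roughly 64–71%. Those gains come mainly from the trainee term. If trainees cannot be identified, the gain is whatever experience and period explain, which the protocol does not tell us.

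**What to change.** Drop the pre-test and name one primary analysis: a linear model on log(TTI) with allocated site, months of experience, and period before or after the COVID-era changes (with the change date defined). Add a random intercept for trainee where a trainee code exists or can be recovered from existing records. Report the ratio of geometric means with its 95% CI, and keep Mann-Whitney as a sensitivity analysis.

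Do not adjust for Cormack-Lehane grade. It is declared after the envelope is opened and the tube marked (Personnel and Technique under {11a}), by a team that is not blinded (section {17a}), so it is a post-allocation measure open to influence.

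**Cost.** There is a little more analysis work. The participant timeline lists no trainee identifier, so codes may have to be retrieved for a trial already under way. The estimand becomes a ratio instead of the difference in means used for sizing. For the 20% target this needs no more patients: with log SD 0.439, a ratio of 1.20 needs 2 × 0.1926 × 8.98 / (ln 1.20)² = 104.1, so 105 per group unadjusted at 85% power, below the planned 149. The amendment should be settled by people who have not seen results by group. This matters because the interim analysis gives the senior-most researcher access to its results.
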